### Outcomes {12}

Cardiorespiratory HealthQuality of life

### Participant timeline {13}

The schedule and plan of the study are illustrated in Fig. 1.

**Fig. 1 Fig1:**
[figure not shown]
Timeline for the proposed study

### Sample size {14}

The sample size was calculated using the formula for comparison of two means. The outcome variable used was VO_2_ max (cardiorespiratory endurance variable) which was taken from a previous study [13]. The details on sample size calculation are as follows for 95% confidence interval and power set at 80%.

$$\begin{array}{c}N=\frac{2(Z{(1-\alpha/2)+\mathrm{Z\beta})}^2\times\mathrm\sigma^2}{\mathrm d^2}\\N=\frac{2{(1.96+0.84)}^2\times5.9^2}{3^2}\\N=\frac{545.82}9\\N=60.6\end{array}$$

Considering the 20% dropout and loss to follow-up, the total sample size was 72 (36 in each group).

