**Methods:**

A total of 60 breast cancer survivors would be included in the study using a randomized controlled allocation of a 2-month physical rehabilitation intervention program with 3 months of follow-up. The intervention would target the cardiovascular endurance component of the participants to improve their physical well-being and quality of life ultimately.

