### Allocation of participants and intervention: randomization and blinding {16a} {16b} {16c} {17a} {17b}

Participants would be allocated to two groups, randomized into equal allocation ratio (1:1) using a simple randomization method through a sealed envelope, with 36 randomized to intervention and 36 to control. Randomization for subject allocation would be double-blinded (conducted by a third party not involved in research) and facilitated through a person not involved in the study. Allocation of intervention will not be blinded and conducted by two researchers in the study FR and WA (physical therapists).

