#### Data analysis {20a} {20b} {20c} {21b}

The data would be analyzed using the SPSS software package version 29. Descriptive and inferential statistics will be done to test the desired hypothesis. Paired and unpaired *t*-tests would be conducted to analyze the changes in the primary outcomes for within and between group analysis. Repeated measures of ANOVA would be done to determine the changes at baseline, end of intervention, and follow-up for the intervention group. If the trial needs to be terminated due to any reasons, interim analysis would be done for the average period of the trial for all participants and the trial would be terminated on a decision from the senior researchers (AH and PK). No adjusted analysis is planned for this research. Missing data would be analyzed through intention-to-treat analysis.

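### The sample-size formula gives about 61 per group, but the plan uses it as the trial total, so power for the stated difference is about 47–57%, not 80%

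*Protocol article*

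**What the plan says.** Section {14} of the protocol article names the method: "The sample size was calculated using the formula for comparison of two means". The sizing variable is VO2 max, with inputs from a cited earlier study, and the error rates are given as: "The details on sample size calculation are as follows for 95% confidence interval and power set at 80"%. The formula is printed in full as N = 2(Z(1−α/2) + Zβ)²σ²/d², with 1.96, 0.84, σ = 5.9 and d = 3, and ends at N = 60.6. The section closes: "Considering the 20% dropout and loss to follow-up, the total sample size was 72 (36 in each group").

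The allocation section repeats the split, "with 36 randomized to intervention and 36 to control". The abstract gives a different number: "A total of 60 breast cancer survivors would be included in the study". The data analysis section plans the between-group comparison as an unpaired t-test ("Paired and unpaired *t*-tests would be conducted to analyze the changes in the primary outcomes for within and between group analysis") and adds: "No adjusted analysis is planned for this research".

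**The concern.** In the two-means formula the factor 2 arises because the variance of a difference between two independent means is 2σ²/n, where n is the size of one group. Solving for n gives a per-group number, so 60.6 means 61 women in each arm. The plan's 72 can be rebuilt only as 60 × 1.2, with 60 taken as both arms together. The abstract's total of 60 and the 36/36 split fit that reading, so it is not a stray misprint.

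The protocol therefore tells readers and the ethics committee that the trial has an 80% chance of detecting a 3-unit difference in VO2 max, when its design offers roughly even odds. A non-significant result could then be misread as evidence that the programme does not work.

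**Working it through.** **Inputs, all from section {14} unless noted.** Difference d = 3; SD σ = 5.9; two-sided α = 0.05 (1.96); power 80% (0.84); allowance for loss 20%; 36 per group (also in the allocation section). Test: unpaired t-test without adjustment (data analysis section).

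**1. Reproduce the plan's figure.** 2 × (1.96 + 0.84)² × 5.9² = 2 × 7.84 × 34.81 = 545.82, and 545.82 / 9 = 60.65. This matches the printed 60.6, so the arithmetic up to this point is right.

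**2. Identify what the 60.65 counts.** With n per group, the standard error of the difference is σ√(2/n). Setting d = (1.96 + 0.84) × σ√(2/n) and solving gives n = 2(1.96 + 0.84)²σ²/d², which is the printed formula. Its result is therefore per group: 61 by the normal approximation, 62 by the exact t-test. A formula for the trial total would carry a 4 in place of the 2 and give 121.3.

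**3. Rebuild the 72.** 60 × 1.2 = 72, split 36/36. Before losses the plan thus has 30 per group.

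**4. Power of the planned design.** Two-sided 5% unpaired t-test, noncentral t, noncentrality d / (σ√(2/n)). The detectable difference is the true difference that gives 80% power.

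| Evaluable per group | Noncentrality | Power for 3 units | Detectable difference, normal formula | Detectable difference, exact t |
|---|---|---|---|---|
| 36 (no loss) | 2.157 | 56.7% | 3.9 | 3.95 |
| 30 (total of 60) | 1.969 | 49.1% | 4.3 | 4.34 |
| 28.8 (36 × 0.8) | 1.930 | 47.5% | 4.4 | 4.43 |

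For comparison, 62 per group gives 80.2%. The normal approximation gives 57.8%, 50.4% and 48.8% for the three rows, so the choice of method matters little.

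**5. Other readings tried.** One-sided testing needs 48 per group and gives only 69.6% with 36 per group (normal approximation); it also conflicts with the printed 1.96. For 90% power, two-sided, 82 per group are needed. None of these leads to 30 or 36 per group.

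**6. Allowance for loss.** Multiplying by 1.2 does not protect against 20% loss: 72 × 0.8 = 57.6, below the plan's own 60. Dividing is correct: even with 60.6 read as the total, 60.6 / 0.8 = 75.8. With the per-group reading, 61 / 0.8 = 76.25, so 77 per group and 154 randomised (62 / 0.8 = 77.5, so 78 per group and 156, by the exact t).

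**The case against.** The strongest reply is that the 47–57% depends on 5.9 being the SD of whatever is compared. The data analysis section speaks of changes in the outcomes, so the unpaired test may be run on change scores, and the document does not say whether 5.9 is the SD of a single measurement or of a change. If it is already the SD of change, the figures above stand. If it is a single-time SD, the SD of change is 5.9 × √(2(1 − r)), where r is the correlation between baseline and follow-up. No document gives r. Over an assumed range, power at 28.8 per group is:

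| Assumed r | Power, change score |
|---|---|
| 0.3 | 36% |
| 0.5 | 47% |
| 0.7 | 69% |
| 0.8 | 85% |

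So 80% after losses could be reached, but only with a high correlation that the plan neither states nor uses. The point that power is conditional stands. It does not rescue the 80% claim, because section {14} derives that claim from 5.9 directly, with no correlation. Adjustment for baseline cannot be called on either, since the plan rules out adjusted analysis.

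It is also fair to say that the dropout arithmetic and the abstract's 60 are minor. The first moves the total from 72 to about 76, and the second looks like the figure before inflation. Neither would be serious alone.

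**Conclusion.** The concern holds. A per-group sample size was used as the trial total, and the stated 80% power does not follow from the printed formula and the 72 patients. On the plan's own inputs (difference 3, SD 5.9 for the compared quantity, two-sided 5%, unadjusted t-test), power runs from 57% with no loss to 47% after the planned 20% loss. The difference and SD come from a cited study that is not shown and are taken as given. This must be corrected, because it concerns the central justification of the trial's size. The loss allowance and the mismatch between 60 and 72 are side corrections to make at the same time.

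**What to change.** In section {14}:

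- State that the formula gives 61 per group (122 evaluable in total), not 60.6 in total.
- Either keep 72 and say what it delivers: with about 29 evaluable per group after 20% loss, about 47% power (unadjusted t-test) for 3 units, or 80% power for about 4.4 units. If 4.4 units becomes the target, say why a difference of that size is relevant. Or keep 3 units at 80% power and raise the target to 154 randomised (77 per group). The investigators must choose between these; rewording corrects the claim but does not raise the power.
- Apply the 20% allowance by dividing by 0.8.
- Say whether 5.9 is the SD of a single measurement or of change, and whether the unpaired test uses follow-up values or changes.

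In the abstract, make the number to be included agree with section {14} and the allocation section.

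The investigators could also restate power for a baseline-adjusted comparison. This would mean changing the statement that no adjusted analysis is planned, and 5.9 would have to be a single-time SD. The assumed correlation must be shown: at 28.8 per group, with SD 5.9 × √(1 − r²), power is about 59% at r = 0.5, 66% at 0.6, 76% at 0.7 and 89% at 0.8.

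Keeping 72 costs only wording in section {14} and the abstract, and a less favourable power statement. Keeping 80% power for 3 units costs 82 more randomised patients (154 − 72).

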### Enrollment, intervention, and recruitment plan {15}

The participants in the study would be recruited under the purposive sampling method. In addition, hospitals from all emirates would be contacted for sharing the contacts of potential participants from the medical records to meet the target sample size. The study follows the Standard Protocol Items Recommendations for Interventional Trials (SPIRIT) guidelines (Fig. 2) [14]. The recruitment of participants will be illustrated using the CONSORT flow diagram [15].

**Fig. 2 Fig2:**
[figure not shown]
Schedule of enrolment and interventions for the protocol

### Allocation of participants and intervention: randomization and blinding {16a} {16b} {16c} {17a} {17b}

Participants would be allocated to two groups, randomized into equal allocation ratio (1:1) using a simple randomization method through a sealed envelope, with 36 randomized to intervention and 36 to control. Randomization for subject allocation would be double-blinded (conducted by a third party not involved in research) and facilitated through a person not involved in the study. Allocation of intervention will not be blinded and conducted by two researchers in the study FR and WA (physical therapists).

### Data collection {18a}

Data will be collected using the data collection sheet which would focus on the demographics and primary outcome variables using reliable and valid tools. Cardiorespiratory health will be evaluated by analysis of the submaximal VO_2_, peak exercise minute ventilation, and direct maximal voluntary ventilation. The 2-km walk test (UKK walk test, Tampere, Finland) would be done along to calculate the submaximal VO_2_ max and spirometry will be done to record the ventilation values measured using Cosmed Fitmate Pro [16–18]. The QoL will be assessed with the European Organization for Research and Treatment of Cancer Quality of Life Questionnaire (EORTC QLQ-C30) (version 3) [19].

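### No single primary variable or time point is named, although the sample size rests on VO2 max alone

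*Protocol article*

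**What the plan says.** All places are in the protocol article.

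- **Outcomes {12}** consists of two items, which the extracted text runs together: "Cardiorespiratory HealthQuality of life". It gives no variable, ranking or time point.
- **Data collection {18a}** says the data sheet will "focus on the demographics and primary outcome variables using reliable and valid tools". It then lists three measures of cardiorespiratory health: submaximal VO2, "peak exercise minute ventilation, and direct maximal voluntary ventilation". Quality of life is to be measured with the EORTC QLQ-C30, and no scale or summary score is selected.
- **Follow-up {18b}** refers to the primary outcome in the singular, with assessments at baseline, 2 months and 5 months.
- **Data analysis {20a}** says that paired and unpaired t-tests "would be conducted to analyze the changes in the primary outcomes for within and between group analysis". It gives no significance level.
- **Sample size {14}** uses one variable: "The outcome variable used was VO_2_ max (cardiorespiratory endurance variable) which was taken from a previous study". The level (95% confidence, z = 1.96) and the power (80%) appear only here.

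On the VO2 variable itself, {18a} first names submaximal VO2. It then says that the 2-km walk test "would be done along to calculate the submaximal VO_2_ max". No secondary outcome is named anywhere in the article.

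**The concern.** The sample size spends a two-sided 5% error rate once, on one variable. The outcome and analysis sections do not carry that choice forward. At least four measures stand under a heading that speaks of primary outcome variables, and none of them is given another status. Run as written, any of several between-group tests could be presented as the trial's main result, and the choice could be made after the data are seen.

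A second, separate matter is whether the SD of 5.9 and the difference of 3 belong to the variable that will be analysed, since the VO2 term changes between sections.

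**Working it through.** **1. The variable the trial was sized on.** Inputs from Sample size {14}: SD 5.9, difference 3, z values 1.96 and 0.84.

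2 × (1.96 + 0.84)² × 5.9² / 3² = 545.82 / 9 = 60.65

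This agrees with the printed 60.6. The formula gives a number per group. How the article moves from it to a total of 72 is a different point and is not argued here. What matters is that α = 0.05 two-sided is used once, for VO2 max.

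**2. How many tests could be called primary.** The article does not fix the number k, so two readings are shown:

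- k = 2: one test for each construct in {12}.
- k = 4: the three cardiorespiratory measures in {18a} plus one QLQ-C30 score. That there is only one score is an assumption.

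**3. Chance of at least one false positive among the between-group tests at one visit**, each at 5%, with no true effects and independent tests: 1 − 0.95^k.

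- k = 2: 1 − 0.9025 = 9.75%
- k = 4: 1 − 0.8145 = 18.5%

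**4. Allowing for correlation.** This was simulated with 200,000 draws of k equally correlated standard normal test statistics, rejecting when |z| > 1.96:

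| k | ρ = 0 | ρ = 0.3 | ρ = 0.5 | ρ = 0.7 | ρ = 0.9 |
|---|---|---|---|---|---|
| 2 | 9.7% | 9.5% | 9.0% | 8.4% | 7.0% |
| 4 | 18.6% | 17.5% | 15.5% | 13.1% | 9.5% |

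The article gives no correlations, so ρ is an assumption shown as a range. Every cell exceeds 5%.

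**5. Keeping four primaries instead.** Bonferroni gives α = 0.05 / 4 = 0.0125, z = 2.50. The number per group becomes 2 × (2.50 + 0.84)² × 5.9² / 3² = 86.3, so 87, against 61 for a single test. At the planned 36 per group, the standard error is 5.9 × √(2/36) = 1.39 and 3 / 1.39 = 2.16. Power is then Φ(2.16 − 2.50) = 37%, against Φ(2.16 − 1.96) = 58% for one test at 5%. The gap between 58% and 80% belongs to the sample-size point set aside in step 1. The drop from 58% to 37% is the price of four primaries.

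**6. The VO2 terms side by side.**

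| Section | Term |
|---|---|
| {14} | VO2 max |
| {18a}, list of measures | submaximal VO2 |
| {18a}, walk test | submaximal VO2 max |

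If the walk test yields an estimate of maximal uptake, it estimates the variable in {14}. If uptake at a submaximal workload is meant, that is a different quantity, and 5.9 and 3 were not planned for it. The wording allows both.

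**The case against.** The strongest reply is that much of this could be settled in a full protocol or analysis plan that is not shown. For a multiplicity rule, a stated α or a success criterion, that reply stands, and their absence is not held against the article. It does not cover the choice of primary endpoint. The article has a section for outcomes, fills it with two unranked constructs, and then uses the primary outcome in both singular and plural.

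A reader might infer several stronger claims that the text does not support:

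- *Every measure is declared primary.* No sentence labels each one. The plural in {20a} could mean only the two constructs in {12}, which is why k = 2 is shown.
- *Each is tested at 5% and the error rate is uncontrolled.* The 5% level is inferred from {14}, and control could be specified elsewhere.
- *Between-group tests are repeated at 5 months.* {18b} mentions the later follow-up for the intervention group, and {20a} limits the three-time-point ANOVA to that group. A 5-month comparison between groups is not clearly planned, so only one visit is counted. Paired within-group tests do not address the randomised contrast and are not counted either.
- *The error rate is far above 19%.* Adding physical, mental and social well-being as three separate tests gives 1 − 0.95^6 = 26.5%. However, those domains come from a statement of expected benefits in the Abstract and Discussion, not from the analysis plan. The article gives no count of questionnaire scores, so a larger k would be a guess.
- *The VO2 mismatch raises the false-positive rate.* It does not. It affects the planning SD, the difference and hence the power. The walk-test sentence can fairly be read as VO2 max estimated from a submaximal test.

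It is also fair to say that {14} already makes VO2 max the natural lead variable. The protocol only needs to say so.

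**Conclusion.** The narrow point holds: the article fixes no single primary variable and no primary time point, although it sizes the trial on one variable. If the outcomes are each tested at two-sided 5%, the chance of at least one false-positive between-group result at one visit is about 10% for two independent tests and 19% for four. For four tests it falls to about 16% at correlation 0.5 and 10% at 0.9. These figures rest on the level implied by {14}, on one quality-of-life score being tested, and on a single visit.

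The VO2 naming is a separate and smaller matter: terms to reconcile, so that the planning figures attach to a named analysis variable. Both points should be settled before outcome data are examined. Neither shows that the trial's error rate is in fact uncontrolled, because an unseen analysis plan may deal with multiplicity.

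**What to change.** In Outcomes {12}, name one primary endpoint: the between-group comparison, at the end of intervention (2 months), of the VO2 max estimate from the 2-km walk test on which {14} is based, at two-sided 5%. Label the ventilation measures and quality-of-life scores secondary, reported with confidence intervals and without a confirmatory claim. Use the same VO2 term in {14} and {18a}, and make the references to the primary outcome in {18a}, {18b} and {20a} agree with {12}.

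One primary test at one time point brings the error rate for the trial's main conclusion back to 5% without splitting α. A hierarchical test of one named quality-of-life score after the primary is possible but optional.

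The cost is mainly wording, with two real consequences. Quality-of-life and ventilation results can no longer carry the trial's conclusion alone. And because ethical approval dates from May 2023 and recruitment was due to begin in September 2023, the change has to go through the amendment route in {25}.

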### Follow-up {18b}

All participants in the intervention group would be followed up after 3 months of training sessions. The demographics and primary outcome would be reassessed to analyze the effects on the baseline, at the end of intervention after 2 months and follow-up at 5 months. Any adverse effects at the time of follow-up would also be recorded.

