### Objective {7}

The objective is to analyze the changes in cardiovascular endurance and QoL domains for breast cancer survivors in the United Arab Emirates using a structured physical rehabilitation program for 2 months with a follow-up after 3 months.

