### Trial design {8}

Prospective, parallel-group, controlled, equal allocation ratio, randomized controlled trial of breast cancer survivors (hospitalized or homecare).

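### As written, the 5-month follow-up and the three-visit ANOVA cover the intervention group only, so the follow-up part of the objective has no randomised comparison

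*Protocol article*

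**What the plan says.** Trial design {8} describes a "Prospective, parallel-group, controlled, equal allocation ratio, randomized controlled trial of breast cancer survivors". Objective {7} is to analyse changes in cardiovascular endurance and quality of life "using a structured physical rehabilitation program for 2 months with a follow-up after 3 months", so the follow-up belongs to the objective.

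Follow-up {18b} then states: "All participants in the intervention group would be followed up after 3 months of training sessions". Its next sentence lists reassessment at baseline, "at the end of intervention after 2 months and follow-up at 5 months", and names no group.

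Data analysis {20a} plans two kinds of analysis. Paired and unpaired t-tests "would be conducted to analyze the changes in the primary outcomes for within and between group analysis"; no visit is named for them, and they are not restricted to one arm. For the three visits the plan is: "Repeated measures of ANOVA would be done to determine the changes at baseline, end of intervention, and follow-up for the intervention group". This is the only analysis that names the follow-up visit. The same section adds: "No adjusted analysis is planned for this research".

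Interventions {11a} gives the control group routine life and standard hospital care, with no assessment schedule.

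**The concern.** Randomisation protects a conclusion only where both arms are measured and compared. If controls are not assessed at 5 months, no between-group contrast can be computed at that visit, and the follow-up result is a before-after change in the trained women.

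The participants have been through chemotherapy and mastectomy and are cleared for rehabilitation (Eligibility criteria {10}), so some recovery without the programme is plausible. Endurance is measured with a repeated 2-km walk test (Data collection {18a}), so retest learning is plausible too. Both would also occur in controls, and a one-arm analysis cannot subtract them. At stake is whether the trial can say that the benefit lasts beyond the programme. Control visits that were never held cannot be recovered at the analysis stage.

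**Working it through.** The main point is structural, so the sections come first.

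| Item | 2 months | 5 months |
|---|---|---|
| Intervention group assessed | Yes, {18b} | Yes, {18b} |
| Control group assessed | Implied by the between-group t-test, {20a} | Not stated in any section shown |
| Between-group test | Unpaired t-test, no visit named | Not possible without control data |
| Three-visit ANOVA | Intervention group only | Intervention group only |

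The expected change from baseline in the intervention arm is the exercise effect plus the change those women would have had anyway. The control arm estimates the second term. With no control observation at 5 months, that term cannot be estimated there.

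**The plan's own figure.** Sample size {14} uses SD 5.9, difference 3, and 1.96 and 0.84 for two-sided 5% and 80% power: 2 × (1.96 + 0.84)² × 5.9² / 3² = 545.82 / 9 = 60.6. The arithmetic reproduces. For a comparison of two means this formula gives the number per group, whereas the plan treats it as the total and enlarges it to 72 (60 × 1.2), 36 per group. That is a separate problem, but it sets the power of a corrected 5-month comparison.

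**Power of a two-arm comparison at 5 months.** Power = Φ(d / (σ√(2/n)) − 1.96), with d = 3 and σ = 5.9.

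- n = 36 per arm: standard error 5.9 × √(2/36) = 1.391; 3 / 1.391 = 2.157; Φ(0.197) = 58%.
- n = 28 per arm (about 20% loss; 36 × 0.8 = 28.8): standard error 5.9 × √(2/28) = 1.577; 3 / 1.577 = 1.903; Φ(−0.057) = 48%.
- Difference detectable with 80% power, 2.8 × 5.9 × √(2/n): 3.9 with 36 per arm, 4.4 with 28.

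These figures take 5.9 as the SD of the quantity compared. If 5.9 is the SD of a single measurement, the SD of a change is 5.9 × √(2(1 − ρ)). That equals 5.9 at a between-visit correlation ρ of 0.5 and is smaller above it, so power for change would then be higher. The protocol gives no ρ.

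**Illustration only: how a one-arm test behaves under shared drift.** Assume no exercise effect, 36 women, ρ between 0.5 and 0.8, and a drift of 1 or 2 VO2 max units common to both arms. Neither ρ nor the drift is in the documents. The standard error of the mean change is 5.9 × √(2(1 − ρ)) / √36, which is 0.983 at ρ = 0.5 and 0.622 at ρ = 0.8. By the normal approximation, a two-sided 5% test of baseline against 5 months is significant in 17% to 36% of trials with a drift of 1 unit, and in 53% to 90% with a drift of 2 units. This shows the mechanism and does not estimate what will happen in this trial.

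**The case against.** The strongest reply is that the text may simply be loose. The second sentence of {18b} names no group, the unpaired t-test has no stated visit, and the timeline and schedule figures, where control visits would appear, are not shown. Controls may well be intended to attend at 5 months. This stands as a limit on certainty. It does not remove the point: {18b} and {20a} both restrict follow-up to the intervention group, and even if controls attend, the three-visit ANOVA leaves their data out. The text needs correction either way.

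A second reply is that follow-up was only ever meant to describe maintenance in the trained arm, since Objective {7}, the abstract's Methods and Interventions {11a} all mention it alongside the programme. That is a fair reading, and neither the objective nor the abstract says that all survivors are followed. A maintenance result of that kind is still uncontrolled and should be labelled so.

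A reader might also infer more than the article supports:

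- That the trial has no randomised comparison at all. It does: the unpaired t-test compares the groups, and the 2-month contrast is unaffected.
- That the paired t-tests ignore controls. Only the ANOVA is restricted to one arm.
- That the protocol plans to claim efficacy from within-arm change. It says only that the ANOVA determines changes; such a claim would be a misuse, not a stated plan.
- That regression to the mean inflates the result. Eligibility criteria {10} selects on no extreme fitness or quality-of-life value.
- That the bias is a known share of the 3-unit target. Any such share is an assumed drift divided by 3.

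**Conclusion.** The point holds for the 5-month visit. Followed as written, {18b} and {20a} leave the follow-up part of the objective without a randomised comparison, and any durability result is an uncontrolled before-after change. The 2-month between-group comparison is intact. The conclusion rests on the stated wording and on the absence, in the text shown, of any 5-month control assessment; the unseen figures could show that controls attend. The size of the possible bias is unknown, because the documents give no figure for change in untreated women. If both arms are compared at 5 months, power is about 48% to 58% at a difference of 3 and an SD of 5.9 for the quantity compared, so a non-significant 5-month result would be weak evidence that the effect had faded.

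**What to change.** In Follow-up {18b}, state that all randomised participants in both groups are assessed at baseline, 2 and 5 months with the walk test, spirometry and questionnaire already planned. In Data analysis {20a}, replace the intervention-only ANOVA with a between-group comparison at 2 and 5 months, and make the within-group paired tests descriptive. A two-arm group-by-time model would do this, but it is not essential: the unpaired t-test on change, specified at each visit, also gives a valid randomised contrast and fits the present rule against adjusted analysis. A baseline-adjusted comparison would require that rule to be changed.

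The cost is one repeat of existing assessments in about 36 controls. The change does not cure the limited power, which should be acknowledged when the 5-month result is interpreted.

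If controls will not be seen at 5 months, restrict the efficacy conclusion to the 2-month between-group difference and label the 5-month result as uncontrolled. That costs only wording.
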